### Data collection methods

Data will be collected through online (Google Forms) reliable and validated questionnaires, as well as via IN or ON field test assessments. Training for assessors will be provided to promote data quality. Table 1 includes the description of trial instruments. Data collection forms will be accessed by assessors, principal investigators (PIs) and data analysts. Data will be securely stored and managed following established ethical guidelines. Data from participants who do not complete at least 80% of the scheduled sessions will be considered a loss to follow-up.

### Plans to promote participant retention and complete follow-up

Plans to promote retention include the above-mentioned motivational strategies. Moreover, they will be informed about the study’s objectives and dissemination plans. Participants who discontinue or deviate from intervention protocols will be contacted by telephone to provide qualitative feedback and help us understand context-specific issues.

### Trial monitoring

The steering group of the research team comprises the PI and senior researchers who participated in planning and will provide organisational support to the trial by involving and supervising students, as well as organising scientific events related to the project. This group will meet every other month. The PI and junior researchers of the team will lead the trial. This group will meet every other week. The PI will be responsible for monitoring trial conduct.

### Statistical methods for primary and secondary outcomes

Demographic data (age, weight, gestational age, area of residence and date of birth) will be described using frequencies and percentages for categorical variables.

Descriptive statistics (mean, SD, median and IQR) will be used to summarise baseline characteristics of participants in both groups (IN and ON).

Descriptive and inferential statistics will be applied to all outcomes.

A comparative analysis of IN *versus* ON interventions will be conducted using both intention-to-treat and per-protocol approaches. Comparative analysis will be used to compare changes in primary and secondary outcomes between IN and ON groups over time (baseline and postintervention). Subgroup analyses will evaluate potential differences between maternal age groups (<35 *vs* 35+ years) and PA level groups.

Adherence to the intervention (proportion of attendance in the planned sessions) will be calculated after the postintervention assessments.

Data from participants who do not complete at least 80% of the scheduled sessions will be considered a loss to follow-up.

Regarding additional outcome analysis, the evaluation of interventions and resources will be performed through descriptive analysis, summarising satisfaction with resources and exercise interventions.

Continuous variables will be assessed for normality using Shapiro–Wilk tests. Normally distributed variables will be presented as mean±SD and analysed using the independent sample t-test. The non-normally distributed data will be reported as the median with IQR and will be analysed using the Mann–Whitney test. For the within-group difference, normally distributed variables will be calculated with the paired-sample t-test. In contrast, those non-normally distributed variables will be calculated with the paired-sample non-parametric Wilcoxon test. Categorical data will be analysed using Pearson’s χ^2^ test or Fisher’s exact test, as appropriate.

A significance level of 0.05 (alpha level) will be set for all statistical tests. Power calculations were performed to ensure that the study was adequately powered to detect clinically significant differences between groups. All statistical analyses will be conducted in Statistical Package for the Social Sciences.

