We hypothesised that a multicomponent supervised prenatal physical exercise programme previously described in Santos-Rocha *et al*’s study^14^ positively impacts PA, fitness, lifestyle and health parameters of women throughout pregnancy, regardless of the delivery environment (in-person (IN) *vs* online (ON)), maternal age or weekly volume of PA, and that both exercise environments are equally effective.

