### Objectives

To describe the study protocol of the ACTIVE PREGNANCY trial following the updated Standard Protocol Items: Recommendations for Interventional Trials 2025 guidelines,^15^ which is a supervised multicomponent prenatal exercise programme delivered either IN or ON aimed at improving maternal PA levels, health-related and functional fitness, healthy lifestyle and health parameters throughout pregnancy, regardless of maternal age or baseline PA. The primary objectives are to compare the impact of IN *versus* ON interventions on PA levels, self-perceived fitness and health-related and functional fitness. The secondary objectives are to assess the impact of both interventions on lifestyle (ie, Mediterranean diet, sleep quality, happiness and depression) and health parameters (ie, weight gain, gestational diabetes or hypertension) and to analyse differences by maternal age subgroups (<35 *vs* 35+years) and weekly volume of PA (<150, 150–300 or 300+min/week). Additional objectives include exploring participant satisfaction with the exercise interventions and evaluating the usefulness of digital resources (ie, ACTIVE PREGNANCY Guide, YouTube channel ACTIVE PREGNANCY and the framework of the ACTIVE PREGNANCY app).

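### None of the listed tests estimates whether the in-person versus online difference varies by subgroup, or compares three PA groups on a continuous outcome

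*Protocol article*

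**What the plan says.** The hypothesis (Protocol article, Background and rationale) is that the programme helps irrespective of delivery mode, "maternal age or weekly volume of PA, and that both exercise environments are equally effective". The Objectives section makes differences by subgroup a secondary objective. Age has two groups, divided at 35 years, and PA has three: "weekly volume of PA (<150, 150–300 or 300+min/week".

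Under Statistical methods for primary and secondary outcomes, one sentence covers this objective: "Subgroup analyses will evaluate potential differences between maternal age groups" and PA level groups. A later paragraph of the same section names the tests:

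- Between groups, continuous and normal: "Normally distributed variables will be presented as mean±SD and analysed using the independent sample t-test".
- Between groups, continuous and non-normal: "will be analysed using the Mann–Whitney test".
- Within group: "normally distributed variables will be calculated with the paired-sample t-test", with the Wilcoxon test if non-normal.
- Categorical: "Categorical data will be analysed using Pearson’s χ^2^ test or Fisher’s exact test, as appropriate".

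The section names no regression model, interaction term, analysis of variance or Kruskal-Wallis test. It also does not say which of the listed tests is meant for the subgroups.

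**The concern.** A claim that an effect holds whatever the woman's age or activity level is a claim about how effects compare across subgroups. It needs an estimate of the difference between subgroup effects, with its uncertainty. The listed tests give a p-value inside a subgroup, or a comparison of two subgroups with the arms pooled. They do not say how far the in-person versus online difference changes from one subgroup to another.

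If the analysts keep to the list, two errors are open to them. One subgroup may reach significance and the other not, purely because they differ in size, and this may be reported as a difference in effect. Or a non-significant result in a small subgroup may be taken as support for consistency, which is the hypothesised result. Either would put a wrong subgroup statement into a trial meant to inform exercise guidance.

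**Working it through.** **1. Objective against tests.**

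| Question | Listed test that answers it |
|---|---|
| Does the in-person versus online difference vary by age or PA group? | None |
| Do the three PA groups differ on a continuous outcome? | None (the t-test and Mann-Whitney take two groups) |
| Do the three PA groups differ on a categorical outcome? | Chi-square or Fisher |
| Do women under 35 and women 35 or over differ in change, arms pooled? | t-test or Mann-Whitney |
| In-person versus online inside one subgroup | t-test or Mann-Whitney |
| Change from baseline inside one subgroup | Paired t or Wilcoxon |

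**2. Inputs for the illustration.** The protocol gives no figure for the subgroup analyses, so there is none to reproduce. From the Sample size section come 36 women for the one-group pre-post comparison, 59 per group for the two-group comparison, power 0.8, alpha 0.05, 100 per arm and 20% loss. The means and SDs behind 36 and 59 are not printed. Solving backwards with the noncentral t, two-sided:

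- 36 pairs imply a standardised pre-post change dz = 0.48.
- 59 per group imply a standardised difference d = 0.52.

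Assumptions: 100 × 0.80 = 80 analysed per arm; 30% aged 35 or over (24 versus 56 women per arm), varied from 40% (32 versus 48) to 20% (16 versus 64).

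**3. Pre-post tests within one arm, same true dz = 0.48 in both age groups.** With powers p1 and p2, the chance that exactly one test is significant is p1(1 − p2) + p2(1 − p1).

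| Women 35+ / under 35 | Power 35+ | Power under 35 | Disagree |
|---|---|---|---|
| 32 / 48 | 0.749 | 0.903 | 30% |
| 24 / 56 | 0.615 | 0.942 | 40% |
| 16 / 64 | 0.435 | 0.966 | 56% |

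For the middle row: 0.615 × 0.058 + 0.942 × 0.385 = 0.036 + 0.362 = 0.398.

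**4. In-person versus online tests inside each stratum.**

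- No true difference (d = 0), two strata: 2 × 0.05 × 0.95 = 9.5%. Three strata: 1 − 0.05³ − 0.95³ = 14.3%.
- If d were 0.52 in every stratum, with 24 and 56 per arm: powers 0.422 and 0.779, so 0.422 × 0.221 + 0.779 × 0.578 = 54%.
- If d were 0.52, with three equal PA groups of 27 per arm: power 0.467 each, so results are mixed in 1 − 0.467³ − 0.533³ = 75%.

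**5. What an interaction estimate could show.** In SD units, SE = √(2/n1 + 2/n2), and the difference in effect detectable with 80% power is 2.80 × SE.

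- 32 / 48: SE 0.323, detectable 0.90 SD.
- 24 / 56: SE 0.345, detectable 0.97 SD.
- 16 / 64: SE 0.395, detectable 1.11 SD.

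For the overall comparison of the arms the figure is 2.80 × √(2/80) = 0.44 SD.

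**The case against.** The strongest reply is that the text assigns no test to the subgroups. The subgroup sentence and the test list stand in different paragraphs, with adherence, loss to follow-up and satisfaction between them. A reader might infer that each subgroup will be tested alone and the p-values compared. The article does not say so, and an analysis plan that is not shown could add an interaction term. This stands, so the point concerns the tests that are named and not a procedure that is written down. It does not remove the point, because the article states its tests one by one and also states an objective that most directly calls for something else.

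A second reply is that the wording can be read more modestly, as benefit inside each group or as a comparison of age groups with each other. On that reading a two-sample test of change by age fits. This stands for age. It does not help for three PA groups on a continuous outcome.

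A reader might also infer that two-sample tests cannot be used with three PA groups at all. That goes too far: an in-person versus online test inside each PA group is legitimate, and chi-square takes three groups for categorical outcomes.

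Finally, d = 0.52 comes from a calculation for exercise against no exercise, while this trial expects the two modes to be equally effective. The 54% and 75% therefore describe a situation the trial does not expect, and 9.5% and 14.3% belong beside them. The pre-post figures are the better illustration, because the trial does expect a change within each arm.

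**Conclusion.** The point holds in a limited form. The named tests contain no estimate of arm-by-subgroup interaction and no comparison of three PA groups on a continuous outcome, although the hypothesis and a secondary objective bear on both. Whether misleading subgroup tests will actually be run cannot be settled from the article.

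If only the listed tests are used, equal pre-post effects in the two age groups would look discordant in about 40% of trials (30% to 56%). For comparisons of the arms, the figure is 9.5% or 14.3% with no true difference, rising to about 54% or 75% if d were 0.52. These figures rest on 80 analysed per arm, an assumed age split (equal thirds for PA), and effect sizes solved back from the stated sample sizes. The mismatch between objective and tests does not depend on them. The matter affects a secondary objective, and the plan should be changed before subgroup results are seen.

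**What to change.** For the subgroup objective, fit for each continuous outcome a linear model with arm, baseline value, site (the randomisation stratum), subgroup (age in two levels, or baseline PA in three) and the arm-by-subgroup interaction. Use an ordinal model for the 1 to 5 self-perceived fitness items. In each subgroup report the in-person versus online difference and the mean change, with 95% confidence intervals. Report the interaction estimate with its 95% confidence interval and label all of this exploratory. State that consistency across age or PA will not be concluded from non-significance. The Objectives section already speaks of baseline PA, so fixing the PA group at baseline only makes that explicit.

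The cost is wording in the analysis plan; no new data are needed. The drawback is wide interaction intervals: for age, only a difference in effect of about 0.9 to 1.1 SD is detectable with 80% power. The trial can therefore describe subgroup effects but can say little about whether they are the same.

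### The claim that benefit does not depend on age or activity is examined only through an age split at 35 and three activity bands, although both variables are held as continuous values

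*Protocol article*

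**What the plan says.** The hypothesis at the end of Background and rationale is that the programme has a positive effect "regardless of the delivery environment (in-person (IN) *vs* online (ON)), maternal age or weekly volume of PA", and that the two environments are equally effective. It therefore makes two claims: benefit holds across age and PA, and in-person (IN) and online (ON) delivery do equally well.

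Objectives makes it a secondary aim to "analyse differences by maternal age subgroups (<35 *vs* 35+years) and weekly volume of PA (<150, 150–300 or 300+min/week". Statistical methods for primary and secondary outcomes carries this forward: "Subgroup analyses will evaluate potential differences between maternal age groups", again cut at 35 years, and between groups defined by PA level. The tests named in that section are the independent t-test or Mann–Whitney, the paired t-test or Wilcoxon, and χ² or Fisher. For between-group comparisons it says: "Normally distributed variables will be presented as mean±SD and analysed using the independent sample t-test". None of these takes age or PA as a continuous modifier.

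The continuous values exist. The same section lists "Demographic data (age, weight, gestational age, area of residence and date of birth", and Table 2 records session duration, weekly frequency, intensity and weekly volume of PA. Eligibility spans 18 to 50 years.

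**The concern.** Cutting age at 35 treats women of 34 and 35 as different and women of 35 and 48 as alike. If the effect of the programme, or the IN–ON difference, drifts with age or PA, a banded comparison is less able to show it than an analysis of the values themselves.

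The direction matters here. The authors expect age and PA to make no difference, so a less sensitive analysis makes the expected result easier to obtain. If a quiet subgroup comparison were taken as support, the lost information would favour the trial's own hypothesis.

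The PA bands have two smaller defects. As written in Objectives, "weekly volume of PA (<150, 150–300 or 300+min/week" places a woman at exactly 300 minutes in two bands. The bands are also in minutes per week, whereas the volume outcome in Table 2 is in MET-minutes per week.

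**Working it through.** **Inputs from the article.** Age cut at 35; PA cuts at 150 and 300 min/week; 100 women per arm with 20% expected loss, so 100 × 0.8 = 80 per arm and 160 analysed. The article gives no figure for information loss or subgroup power, so there is nothing of its own to reproduce on this point.

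**Assumed, because the article gives no distributions.** Age about normal; PA normal with varied band shares, or log-normal; the effect changes linearly with the modifier. The 80% reference power is a benchmark for comparison. The Sample size section powers no interaction.

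**Age: information kept.** For a normal variable split with a share p above the cut, and z the matching normal quantile, the share kept about a linear trend is φ(z)² / [p(1 − p)].

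**Age: power after the split.** If continuous age has 80% power at two-sided α = 0.05, the expected test statistic is 1.96 + 0.84 = 2.80. Power after the split is Φ(2.80 × √kept − 1.96).

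Example with 30% aged 35+: z = 0.524 and φ(z) = 0.3477, so kept = 0.1209 / 0.21 = 0.576 and power = Φ(2.80 × 0.759 − 1.96) = Φ(0.166) = 0.57.

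| Share aged 35+ | Kept | Lost | Power after split |
|---|---|---|---|
| 20% | 49.0% | 51.0% | 50% |
| 25% | 53.9% | 46.1% | 54% |
| 30% | 57.6% | 42.4% | 57% |
| 35% | 60.3% | 39.7% | 59% |
| 50% (best case) | 63.7% | 36.3% | 61% |

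For SD 5 and mean age 31, 32 or 33, the share aged 35+ is 21%, 27% or 34%, and the loss is 49.7%, 44.2% or 39.9%. Over means 29–34 and SDs 4–6 the loss runs from 37% (mean 34, SD 6) to 73% (mean 29, SD 4).

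**PA: three bands.** The share kept is the between-band share of the variance, Σ(φ(a) − φ(b))² / p over bands (a, b).

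| Band shares, normal PA (%) | Lost |
|---|---|
| 27/46/27 (about the best possible) | 19.0% |
| Equal thirds | 20.7% |
| 50/30/20 | 24.3% |
| 60/30/10 | 29.5% |
| 70/20/10 | 37.1% |
| 80/15/5 | 48.1% |

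Simulated log-normal PA with medians 100–250 min/week and log-SD 0.5–0.9 gives losses of 19.5–48% if the effect is linear in log PA and 21–61% if it is linear in raw minutes. On a square-root scale, with medians 150–250 and log-SD 0.7–0.9, the loss is about 21–36%.

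Three bands also need a 2-df test. Where 76–80% of the information is kept, 80% power on continuous PA becomes about 57–60% (non-central F, 154 error df).

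**The case against.** **The percentages depend on shape.** They measure loss about a linear trend. The measure is a squared correlation, so it is symmetric: if the effect truly steps at 35, a linear age term keeps only the share that the split keeps in the table, and the split is the better analysis. The article does not say which shape holds. This stands. It is a reason to check for non-linearity and keep the bands, not a reason to rely on the bands alone.

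**The unseen plan may add a continuous analysis.** Nothing in the article forbids one, and fixing cut points in advance guards against choosing them from the data. This stands too. The point is confined to what the article does fix: the cut points, and a list of tests in which age and PA appear only as groups.

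**The fault may be reading non-significance as sameness.** The article does not say it will read subgroup results that way, and a non-significant continuous interaction could be misread just as easily. Hence the fix asks for estimates with intervals as well as a change of term.

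**Two stronger readings are tempting.** A reader might infer that this trial discards a known share, such as 40–50% of the age information and 20–24% of the PA information. The documents give no mean, SD or share aged 35+ and no PA distribution, so those figures are conditional, and 20–24% for PA lies near the low end. A reader might also infer that the 35+ group falls short of the protocol's own sample sizes of 36 and 59. The 36 is for a one-group before–after comparison. With 21–34% aged 35+, the two arms pooled would have about 34–55 such women among 160 analysed, which mostly reaches it. The 59 is for exercise against no exercise, not for IN against ON.

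**Conclusion.** The point holds as a cheap improvement to a secondary analysis; it does not expose an error or contradiction in the main comparison. For a hypothesis about independence from age and PA, the article names only banded comparisons while holding both variables in continuous form.

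Under normality and linearity, the age split cannot lose less than 36%, whatever share of women is 35 or older, so that conclusion does not hang on a guessed mean age. The size beyond that floor does. The PA loss is about 20% at best and could be much larger if PA is skewed or most women fall in one outer band. If the dependence is a step at 35, the comparison of the two age analyses reverses.

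**What to change.** Make the prespecified effect-modification analysis a model of change from baseline with arm, continuous age, continuous baseline weekly PA and the interactions of age and PA with arm. Fix one PA transformation in advance that allows zero values (a plain logarithm does not), and include a check for non-linearity.

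The interactions address only how the IN–ON difference varies. To cover the other half of the hypothesis, also report the within-programme change across the range. Give both quantities with confidence intervals over the observed ages and PA volumes, and state that a non-significant interaction will not be taken as proof that age or PA does not matter.

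Keep the age split and PA bands as supporting tables, remove the overlap at 300 min/week, and state the PA unit used.

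The cost is a change of wording and some analysis time, with no new data. The downside is an assumption about shape, partly covered by the non-linearity check and the retained bands.

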### Trial design

This is a multicentre, two-arm, parallel-group, randomised controlled trial (RCT) with a 1:1 allocation ratio and an equivalence framework. Pregnant women will be randomly assigned to either an IN or ON supervised multicomponent exercise intervention.

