### Eligibility criteria for exercise professionals who will deliver the interventions

The exercise intervention will be carried out by graduated exercise professionals (EQF level 6 or 7), holders of a BSc, MSc or PhD in Exercise or Sport Sciences, with specialisation in exercise testing and prescription during pregnancy. Exercise professionals will explain the study’s objectives and obtain informed consent before conducting assessments and delivering the exercise intervention.

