### Exercise intervention programmes and comparators

The interventions follow international guidelines for PA during pregnancy.^7^,^9^ The exercise programme was designed and validated as a complex intervention and underwent three stages: development, pilot testing and evaluation.^14^ Exercise sessions consist of a combination of aerobic, resistance, stretching, balance, coordination, postural and pelvic floor muscle exercises, using multicomponent activities, such as aerobics, dancing, step, Pilates, bar, chair and resistance exercises using elastic bands, exercise balls, mats, dumbbells or body weight.

Table 1 describes both arms of the exercise intervention in line with the American College of Sports Medicine exercise prescription guidelines.^17^

**Table 1 T1:** Description of both arms of the exercise intervention

Arm 1:IN exercise group	Type of exercise: multicomponent prenatal exercise programme, including aerobic, coordination, strength, stretching, balance, postural and pelvic floor muscle training exercises.Duration and frequency: two sessions of 60 min per week for 12 weeks.Intensity: moderate. According to the Borg scale of perceived exertion, which ranges from 6 to 20, moderate exercise is rated between 13 and 14. Each pregnant woman will rate her perceived exertion on a scale of 6–20.IN supervision: qualified exercise physiologists.Setting: healthcare, university or fitness centres.
Arm 2:ON exercise group	Type of exercise: multicomponent prenatal exercise programme, including aerobic, coordination, strength, stretching, balance, postural and pelvic floor muscle training exercises.Duration and frequency: two sessions of 60 min per week for 12 weeks.Intensity: moderate. According to the Borg scale of perceived exertion, which ranges from 6 to 20, moderate exercise is rated between 13 and 14. Each pregnant woman will rate her perceived exertion on a scale of 6–20.Remote supervision using a virtual platform: qualified exercise physiologists.Setting: home.
	Examples of the exercise programme are continuously updated on the ACTIVE PREGNANCY YouTube channel:@GravidezAtiva-ActivePregnancy(https://www.youtube.com/channel/UC0Vyookwc0mcQ5T70imtoNA/playlists).

IN, in-person; ON, online.

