### Strategies to improve adherence to interventions

Exercise professionals will monitor adherence to the intervention by recording the number of sessions attended over 12 weeks. Motivational strategies include organising online group meetings, sending weekly WhatsApp and Instagram reminders, providing access to resources promoting an active and healthy lifestyle and offering access to the YouTube channel.

The overall focus of these sessions is based on what already motivates participants to increase or maintain their PA level and healthy lifestyle. This is achieved by fostering interaction among participants to create meaningful group processes, such as support, experience exchange and reflection, as well as collecting feedback regarding the exercise programme and resources. All monthly online sessions will last 20–30 min and are led by exercise and health professionals. These sessions aim: (1) to inform about PA guidelines, benefits associated with PA and possible ways to increase PA during pregnancy; (2) to discuss participant’s barriers, wishes, needs, knowledge and former PA experiences to identify individual characteristics and motivation towards a more physically active lifestyle; (3) to teach the advantages of using a PA tracker, aside from measuring the PA level, the activity trackers are also used as an intervention element to motivate the participants to increase their PA levels, share it on a Strava group and provide feedback on recent PA performances; (4) to collect feedback regarding the organisation of the exercise programme and (5) to discuss other relevant topics chosen by the participants, such as myths about pregnancy PA, postpartum PA, the pelvic floor, uterine contractions, abdominal muscles and diastasis recti, birth, etc.

Individual sessions will be scheduled during the daytime at a time that is as convenient as possible for the participant.

The primary objectives of these motivational strategies are to enhance participant retention and adherence to follow-up, as well as to incorporate a patient-centred approach into the exercise intervention.

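### The planned IN-ON tests treat every woman as independent; if physiologists or classes are specific to one arm, the standard error is too small

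*Protocol article*

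**What the plan says.** All places are in the protocol article.

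- **Design.** Trial design describes the study thus: "This is a multicentre, two-arm, parallel-group, randomised controlled trial (RCT) with a 1:1 allocation ratio and an equivalence framework". The woman is the unit of randomisation: "Pregnant women will be randomly assigned to either an IN or ON supervised multicomponent exercise intervention". The section on assignment and randomisation adds stratification by study site.
- **Delivery.** Table 1 has qualified exercise physiologists supervising both arms. IN sessions take place in healthcare, university or fitness centres. ON sessions take place at home: "Remote supervision using a virtual platform: qualified exercise physiologists".
- **Who assesses.** The eligibility criteria for exercise professionals give the same professional role both tasks: "conducting assessments and delivering the exercise intervention".
- **Between-arm test.** Statistical methods for primary and secondary outcomes states "Normally distributed variables will be presented as mean±SD and analysed using the independent sample t-test" and "The non-normally distributed data will be reported as the median with IQR and will be analysed using the Mann–Whitney test". No term for site, physiologist or class is named. The level is also fixed: "A significance level of 0.05 (alpha level) will be set for all statistical tests".
- **Sample size.** The two-group calculation gives 59 per group for independent groups, with power 0.8 and alpha 0.05. The plan is 100 per group after an expected 20% loss. No allowance for clustering is mentioned.

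**The concern.** Women trained by the same physiologist, or in the same class, tend to have more similar changes than women trained by different ones. The professionals' role also covers assessment, so a provider's way of testing can add to that similarity. The t-test and the Mann-Whitney test ignore it.

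The consequence depends on how providers are spread over the arms. If a physiologist or class belongs to one arm only, provider differences enter the IN-ON contrast as unrecognised noise. A difference between two sets of instructors can then be declared a difference between delivery modes. In a trial with an equivalence framework, an interval that is too narrow can also support a claim of equal effectiveness too easily. A site term alone does not cure this, because it does not remove correlation among women who share a provider within one arm.

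**Working it through.** **Inputs from the article.** Alpha 0.05 (two-sided assumed, since sidedness is not stated); 59 per group; 20% loss; 100 per group planned, hence 100 × 0.80 = 80 per arm with outcome data.

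**Inputs not in the article, so assumed.** ICC 0.02 to 0.10; m = 5 to 20 women per cluster (per arm, where a cluster spans both); total variance 1.

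**1. The plan's own figure.** The mean and SD behind the 59 are not shown, so it can only be inverted. At 80% power and two-sided 0.05 it implies a standardised difference of 0.52: 2 × (1.96 + 0.84)² / 0.52² ≈ 58, which rounds up to 59 with unrounded quantiles. That formula contains no clustering term. Loss alone would need 59 / 0.8 = 74 per group, so 100 leaves a surplus.

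**2. Clusters nested within arm.** Design effect DE = 1 + (m − 1) × ICC. Actual error = 2 × [1 − Φ(1.96 / √DE)].

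Example, m = 10 and ICC 0.05: DE = 1 + 9 × 0.05 = 1.45. The planned standard error is 1/√1.45 = 0.83 of the true one. The error is 2 × [1 − Φ(1.63)] = 10.4%.

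| Women per cluster | ICC 0.02 | ICC 0.05 | ICC 0.10 |
|---|---|---|---|
| 5 | 5.9% | 7.4% | 9.8% |
| 10 | 7.1% | 10.4% | 15.5% |
| 20 | 9.5% | 16.0% | 25.0% |

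Simulating the planned t-test (20,000 runs, 80 per arm, no true difference) agrees: 5.8% to 9.4% at m = 5, 6.9% to 15.2% at m = 10, and 9.5% to 25.3% at m = 20. With no clustering it gives 4.7% to 5.1%. If only one arm is clustered, ICC 0.05 gives about 8% at m = 10 and 10% to 11% at m = 20.

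**3. Physiologists serving both arms in balance.** The common provider effect cancels in IN minus ON. Over the same values of ICC and m, the simulated error is 4.0% to 5.0%, and the planned standard error is 1.00 to 1.05 times the true one.

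**4. Mixed case.** With half the provider variance common to both arms and half arm-specific, m = 10 and ICC 0.05 give 7.5%.

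**5. The error relevant to equivalence.** The article gives no margin, so 0.5 SD is assumed. With the true difference at that margin, two one-sided tests falsely declare equivalence in about 5% of trials without clustering. With nested clusters at m = 10 and ICC 0.05, this is about 9%.

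**6. Effect on numbers.** If DE = 1.45 applied, 59 × 1.45 / 0.8 = 107 per group, against 100 planned.

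**The case against.** The strongest reply is that nothing in the article establishes the harmful structure, and that caseloads and rosters are operational details an article may leave to the full protocol. That is fair, and it limits the point to a conditional one. It does not remove it, because the article itself fixes the tests, and those tests are right only under one family of structures.

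A reader might infer several stronger things that the documents do not support:

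- **That physiologists are shared by both arms and that this shrinks the standard error.** Sharing is not stated. If balanced, it would make the t-test valid or slightly conservative.
- **That exercise is given in group classes.** The phrase "fostering interaction among participants to create meaningful group processes, such as support, experience exchange and reflection" comes from Strategies to improve adherence to interventions, where it describes the motivational meetings, held monthly for 20 to 30 minutes, not the twice-weekly exercise sessions. That section also mentions individual sessions. What does follow is that any shared exercise class would sit within one arm, since IN takes place at a centre and ON at home.
- **That the false-positive rate doubles.** That is one cell of an assumed grid. Over all structures considered, the range is about 4% to 25%, which includes no problem at all.
- **That 80 per arm act like 80 / 1.45 = 55, and so fall short of the required 59.** The 59 comes from a comparison of exercise with no exercise, so it is not a benchmark for IN versus ON. Taken at face value, 55 instead of 59 lowers power only from 80% to about 77%, and the planned 100 absorbs most of the assumed design effect.

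**Conclusion.** The concern holds in conditional form. The fixed tests assume independent women, the treatment is delivered by physiologists at several sites, and the article does not say how physiologists or classes map onto the arms. If they are arm-specific, the nominal 5% error is about 6% to 25% over the assumed grid with both arms nested, and false claims of equivalence rise as well. If physiologists serve both arms in balance, there is no inflation. Every size rests on an ICC and a cluster size that the article does not give, so confidence in the magnitude is low. The analysis is still worth changing, because a model with a provider term is suitable under either structure and the planned tests are not.

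**What to change.** 1. State which physiologists deliver which arm, and whether exercise sessions are shared classes.
2. Record for each woman the physiologist, and the class if shared, to whom she is scheduled at allocation. Defining this by the sessions she later attended would make it a post-randomisation variable, undefined for women who attend none. Scheduled provider is defined for the whole intention-to-treat set.
3. Replace the t-test and Mann-Whitney test for the IN-ON contrast with a linear mixed model of change from baseline. Include arm, site and a random effect for physiologist or class (arm-specific where nested), with Kenward-Roger or Satterthwaite degrees of freedom. Take the estimate and confidence interval, including any interval used for equivalence, from that model.
4. State in the sample-size section that 59 per group assumes no clustering.

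The cost is one field beside the attendance record that the professionals already keep, and revised analysis wording. Recruitment began in May 2025, so the field should be added soon, while provider identity can still be recovered. The downside is wider intervals if clustering is present. They will be notably wider if there are few physiologists per arm, because the provider variance is then poorly estimated.
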